#### 2.4.3. Dietetic Counselling

At the beginning of each dietary phase, participants will meet with a dietitian for 45 min to discuss dietary guidelines. For the MedD phase, participants will be provided with a set of MedD diet guidelines (Appendix A), including serving sizes, guidelines to help incorporate dairy foods into their diet (Appendix B), education on serving sizes of various foods, and a Mediterranean diet recipe book. A weekly semi-quantitative checklist based on that employed in the Medley trial [126] will also be provided to assess adherence and to assist participants in becoming familiar with foods and amounts associated with a MedD diet (Appendix C). The checklist will be filled-in daily, using a tick system (1 tick = 1 serve consumed) and returned at each fortnightly visit. The dietitian will use this information as a discussion point, to assist the participant in following the diet. 

A similar approach will be used to educate participants in following the LFD. Each participant will be provided with a set of guidelines (Appendix D), education on fat content and portion sizes of various foods and a label reading handout (Appendix E), to assist with identifying fat content, including saturated and trans-unsaturated fat, when selecting packaged foods. 

All participants will attend fortnightly appointments throughout the intervention phases to meet with the dietitian and discuss their progress. Participants will be weighed to determine body mass. Should there be any gain, participants will be educated on their dietary choices, satiety, mindful eating and portion sizes. Any difficulties or adverse effects of the diet will be discussed, and strategies will be developed to assist in increasing adherence. Goal setting for the next fortnight, led by the participant with encouragement from the dietitian, will be conducted using the S.M.A.R.T goals for achieving high adherence (S, specific; M, measurable; A, achievable; R, realistic; T, time based).

### 2.5. Outcomes

#### 2.5.1. Blood Pressure

Home measured systolic blood pressure will be the primary outcome. Home blood pressure assessments have stronger predictive power for complications of hypertension and mortality than clinic blood pressure assessments [127,128]. Further, multiple home blood pressure measurements have comparable reliability to ambulatory blood pressure measurements in evaluating hypertension [129]. Participants will be provided with an A&D Company Ltd. digital blood pressure monitor (model UA-767) and instructed to measure their blood pressure and heart rate every morning, afternoon and evening, for a period of six days at each of the four study time-points. Participants will be asked to take measurements at consistent times each day, at least one hour after the consumption of caffeine or alcohol and 30 min after food or exercise. Each measurement of blood pressure will follow a five-minute resting period in the seated position and three readings will be taken, spaced at least one minute apart [130,131]. Home blood pressure will be recorded at four time-points over the course of the trial, one week prior to clinic assessment visits (at pre-baseline, Week 7, Week 15 and Week 23). Blood pressure will also be measured in-clinic using an Omron Healthcare Co. digital blood pressure monitor (model 1A1B Hem-7000-CIL) at the beginning and end of each dietary phase. A similar protocol for in-clinic measurements will be used, with blood pressure and heart rate measurements following a five-minute resting period in the seated position. Three readings will be taken at each visit, spaced at least one minute apart.

#### 2.5.2. Secondary Outcomes

Secondary cardiovascular outcomes will include diastolic blood pressure and heart rate, body mass index (BMI), waist-to-hip ratio, body composition (percentage body fat, lean mass and abdominal adiposity) assessed using dual-energy x-ray absorptiometry (DEXA), fasting blood lipids, CRP, fasting plasma glucose, fasting serum insulin, erythrocyte cell fatty acids and Apolipoprotein E4 (APOEε4). A faecal sample will also be collected to explore the effects of a Mediterranean diet with adequate calcium on gut microbiota.

Fasting venous blood will be collected by venepuncture and centrifuged (4 °C, 4000 rpm, 10 min) before plasma and erythrocytes are separately aliquoted and frozen at −20 °C and then stored at −80 °C. Lipids, CRP, glucose and insulin will be measured at an external NATA accredited laboratory using standard procedures. Insulin resistance will be calculated using The Homeostasis Model Assessment (HOMA2) Calculator v2.2.3 (University of Oxford, Oxford, UK) [132]. This method to determine an insulin resistance score (HOMA2-IR) has been validated in samples with varying degrees of insulin sensitivity, with no differences shown between gender, age, BMI or diabetes status [133]. A higher HOMA2-IR score indicates greater insulin resistance. Participants with fasting insulin levels >57 mU/L, indicating diabetes related metabolic disturbance, will be excluded from these calculations. Erythrocyte fatty acids will be measured using direct transesterification as described by Tu et al. (2013) [134]. APOEε4, an indicator of increased risk for AD, will be determined using the TaqMan^®^ SNP Genotyping assay kit (Applied Biosystems, Warrington, UK) [135].

##### Cognitive Performance, Dementia Risk and Mood

The cognitive domains of interest are verbal and visual memory, processing speed and executive function due to their demonstrated sensitivity to ageing and cardiovascular health, and their known responsiveness to short term nutritional interventions [68,106,136,137,138,139].

A set of cognitive tests from the Cambridge Neuropsychological Test Automated Battery (CANTAB) [140] will be administered to evaluate cognitive function across these domains. The selected tests include Motor Orientation Task (MOT), Paired Associates Learning (PAL), Delayed Matching to Sample (DMS), Verbal Recognition Memory (VRM), Reaction Time (RTI), Rapid Visual Information Processing (RVIP), Spatial Working Memory (SWM), Stockings of Cambridge (SOC) and Attention Switching Task (AST). A description of these tests and the cognitive functions examined by each is presented in Table 1.

The CANTAB offers parallel versions of each test for repeated measures designs to limit effects of learning. The test-retest reliability (*r*) of the chosen tests range from an *r* = 0.54 (RTI) to *r* = 0.87 (PAL) [141]. While test-retest coefficient less than *r* = 0.7 may compromise comparisons between repeated testing [142] the difference between real effects and learning effects can be determined by using standardised scores and their standard errors at each visit [141].

Addenbrooke’s Cognitive Exam-Revised (ACE-R) will be administered to screen for MCI and dementia and to detect change in cognitive function over the course of the trial. The ACE-R assesses attention, orientation, memory, fluency, language and visuospatial abilities and has demonstrated high sensitivity and specificity for detecting both MCI and dementia [120].

Dementia risk will be assessed through the Cardiovascular Risk Factors, Aging and Dementia (CAIDE) score and the Framingham vascular risk score. The CAIDE was developed to predict a 20-year risk of developing late-life dementia from middle age risk profiles [59] and is calculated on the basis of age, sex, education, hypercholesterolemia, systolic blood pressure, physical activity, obesity and apolipoprotein E genotype. The CAIDE has demonstrated high sensitivity (0.81) and moderate specificity (0.61). The Framingham vascular risk score calculates the risk of developing vascular disease based on age, sex, systolic blood pressure, hypertension, HDL cholesterol, total cholesterol, smoking and diabetes [143]. Notably, a higher cardiovascular risk score on the Framingham has been associated with greater declines across cognitive domains [144,145]. Compared to the CAIDE, the Framingham risk score has shown stronger associations with 10-year trajectories of cognitive decline [145].

Psychological well-being will be evaluated through the SF-36 Health Survey [146]. The SF-36 was designed to measure perceived health status through the constructs of vitality, physical functioning, bodily pain, general health perceptions, physical role functioning, emotional role functioning, social role functioning and mental health, and has reported sensitivity to change, high internal consistency, construct validity and adequate test-retest reliability [146]. Further, the SF-36 has demonstrated sensitivity to nutritional interventions [147,148,149]. To measure transient and enduring mood states, the Profile of Mood States (POMS) questionnaire will be employed. The POMS examines the constructs of tension-anxiety, depression-dejection, anger-hostility, vigour-activity, fatigue-inertia, and confusion-bewilderment. The POMS has demonstrated good internal consistency (Cronbach’s alpha = 0.63 to 0.96) and test re-test reliability of *r* = 0.61 to *r* = 0.69 at 6 weeks [150].

##### Diet Adherence

Adherence to the MedD intervention will be assessed using the weekly checklist (Appendix C, described above). Weekly totals of each food group will be compared against dietary guidelines to determine % adherence to the MedD diet. A 14-item Mediterranean diet adherence tool, adapted from the PREDIMED study to align with the Australian food supply and The Australian National Health and Medical Research Council (NHMRC) guidelines for alcohol consumption, will also be completed and returned at each fortnightly visit [61] (Appendix F). Adherence to the LFD will be measured using a 9-item low-fat diet adherence tool adapted from the PREDIMED study, completed and returned at each fortnightly visit [61] (Appendix G). These tools are designed to capture a generalised pattern of consumption relevant to the dietary phase. Finally, a 6-day weighed food record (WFR) will be completed before and during each dietary phase to calculate energy and macro and micronutrients intakes. 

Adherence to the whole dietary phase and the dairy food component of the MedD intervention will be determined at the first fortnight dietetic visit. Participants must meet a minimum of 75% adherence (as determined by checklists) to the relevant dietary prescription and a minimum of 75% adherence to the dairy recommendation (i.e., participants need to consume at least 3 serves dairy products per day to be compliant). If participants are unable to increase adherence above 75% in the next fortnight they will be excluded from the study.

In addition to the 14-point Mediterranean diet adherence tool, information from the 6-day WFR at the beginning and end of each dietary phase will be used to determine foods relevant to the Mediterranean diet, which will be selected and grouped appropriately to calculate adherence to a Mediterranean diet. Adherence will be determined through a modified 15-point score as described by Davis, Bryan, Hodgson and Murphy [49], based on a scoring system described by Trichopoulou, Costacou, Bamia and Dimitrios [54]. Relevant foods will be grouped into; vegetables, fruits, nuts, legumes, fish, breads, cereals, dairy and olive oil. For each of these groups, intakes (as grams/MJ) above the baseline group mean are awarded 1 point. Additional groups for sugars, eggs, potato, meat and miscellaneous are awarded 1 point for intakes below the baseline group mean. Previously the dairy food group was scored negatively (1 point for intakes below the mean) but will now be scored positively (1 point for intakes of 3 serves or more per day). For red wine, intakes of 200 mL per 8.7 MJ or below are awarded 1 point. 

### 2.6. Procedure 

Participants will attend two pre-baseline visits, four clinic assessment visits and six fortnightly visits at the Sansom Institute Clinical Trial Facility. 

Pre-baseline visits will take place one week before each dietary intervention begins. Participants will be provided with information about the study and asked to complete the SF-36, POMS, a six-day WFR and record home blood pressure for six days. The same measures will also be completed in the final week of each intervention at Weeks 7 and 23. 

Clinic assessment visits will take place at Weeks 0, 8, 16 and 24 (See Figure 1) and will include blood pressure measurement, anthropometry, DEXA scan and collection of fasted blood samples. Participants will be instructed to maintain their habitual levels of physical activity over the course of the trial. At each clinic assessment visit participants will be asked to provide details of habitual physical activity undertaken over the previous 2 months, including type of activity, frequency, duration and intensity. At Weeks 0 and 16 participants will be assigned their randomly allocated diet and will meet with the dietitian to discuss dietary guidelines. Participants will then consume a standardised continental breakfast before cognitive measures are administered. 

Fortnightly visits will be conducted throughout the intervention periods. At these visits weight will be measured and participants will have an opportunity to discuss their progress, challenges and goals with the dietician. 

The washout period will take place between the Week 8 and Week 16 clinic assessment visits, separating the two dietary intervention phases. 

Any changes to medications or dietary supplements will be noted throughout the course of the study and factored into the final analysis.

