#### Cognitive Measures

A computerised mode of cognitive testing has been chosen to increase accuracy and reliability in detecting change, especially in instrument sensitive tasks such as reaction time [151]. To limit the influence of potential measurement bias, the administration of cognitive measures will be controlled and standardised across participants and visits, as described by Stonehouse et al. [152]. Cognitive assessments at Weeks 0, 8, 16 and 24 will be conducted at a similar time of day, between 9:30 a.m. and 12:00 p.m. Participants will have completed a 12-h fast from food, beverages (excluding water), caffeine and alcohol before arriving at the clinical trial facility. Following cardiometabolic assessments, anthropometry and DEXA scan, the same continental breakfast will be provided and eaten within 15 min of cognitive testing. If participants have not had an adequate amount or quality of sleep the preceding night cognitive testing will be rescheduled. The testing environment will be controlled with regard to temperature and noise in order to reduce distraction. A CANTAB familiarisation task will be performed at each testing session, and each cognitive task will have a practice component. Further, CANTAB administration will be standardised through use of a testing script provided by Cambridge Cognition.

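### As written, cognitive testing at Weeks 0 and 16 follows diet assignment and the opening dietitian session, steps not described before testing at Weeks 8 and 24

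*Protocol article*

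**What the plan says.** Section 2.6 (Procedure) of the protocol article describes the four clinic assessment visits at Weeks 0, 8, 16 and 24. After listing the clinical measurements it says: "At Weeks 0 and 16 participants will be assigned their randomly allocated diet and will meet with the dietitian to discuss dietary guidelines". The next sentence reads: "Participants will then consume a standardised continental breakfast before cognitive measures are administered".

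Section 2.4.3 (Dietetic Counselling) gives the timing and length of that meeting: "At the beginning of each dietary phase, participants will meet with a dietitian for 45 min to discuss dietary guidelines". The materials handed out and the topics covered differ between the two diets.

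The Cognitive Measures part of section 2.6 states that "the administration of cognitive measures will be controlled and standardised across participants and visits", with the aim of limiting measurement bias. Its own sequence is: "Following cardiometabolic assessments, anthropometry and DEXA scan, the same continental breakfast will be provided and eaten within 15 min of cognitive testing". It mentions neither the assignment nor the dietitian.

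**The concern.** The trial cannot be blinded to diet. If the stated order is followed, participants sit the baseline cognitive tests just after learning (Week 0) or having confirmed (Week 16) which diet they are starting, and after a counselling session specific to that diet, held while they are still fasting. At the end of each phase, no such session comes before the tests. The two ends of each within-phase comparison are therefore measured after different events, and at baseline those events depend on the diet.

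This matters because the plan does not confine itself to end-of-phase scores. Section 2.7 announces a mixed model covering within-subject as well as between-subject effects for cognitive outcomes, and makes a significant change in cognition the trigger for a hierarchical regression on cardiometabolic outcomes. That regression serves the secondary aim in section 1.4.

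**Working it through.** No figure in the protocol needs reproducing. The check compares the described order of events and then traces what a shifted baseline would do.

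**1. Events before cognitive testing, as described**

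| Step | Weeks 0 and 16 | Weeks 8 and 24 | Where stated |
|---|---|---|---|
| Clinical measurements, fasted blood, DEXA | yes | yes | 2.6 |
| Diet assigned | yes | not described | 2.6 |
| Opening dietitian session, 45 min | yes | not described | 2.6 and 2.4.3 |
| Standard breakfast | yes | yes | 2.6 and Cognitive Measures |

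The visit count does not supply a matching session at Weeks 8 and 24: "Participants will attend two pre-baseline visits, four clinic assessment visits and six fortnightly visits". The fortnightly dietitian contacts are counted apart from the clinic assessments. If split equally, they are three per phase (6 / 2 = 3; the equal split is an inference).

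**2. What the standardisation statement covers**

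The Cognitive Measures section fixes the hours of testing ("Cognitive assessments at Weeks 0, 8, 16 and 24 will be conducted at a similar time of day, between 9:30 a.m. and 12:00 p.m"), the 12-hour fast, the breakfast, a sleep check, the room, the familiarisation and practice tasks, and the script. All of these can be met wherever the dietitian session falls. The section therefore neither reverses the order in 2.6 nor is strictly contradicted by it; it leaves the position of two steps open.

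**3. Effect of a shifted baseline**

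Let b_M and b_L be the shifts, in SD units, that the preceding steps cause in the measured baseline under the Mediterranean and low-fat diets, on a scale where higher is better.

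- Bias in within-phase change = −b_M or −b_L.
- Bias in the between-diet difference of changes = −(b_M − b_L).
- Bias with baseline as a covariate with slope β = −β(b_M − b_L).
- Bias in a comparison of end-of-phase scores only = 0.

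The documents give no value for b. The values below are assumptions, set against the 0.5 SD effect in section 2.7.

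| b_M | b_L | Within-phase bias (M; L) | Between-diet bias, change scores | Size as share of 0.5 SD |
|---|---|---|---|---|
| 0.1 | 0.1 | −0.1; −0.1 | 0 | 0% |
| 0.2 | 0.2 | −0.2; −0.2 | 0 | 0% |
| 0.1 | 0 | −0.1; 0 | −0.1 | 0.1 / 0.5 = 20% |
| 0.2 | 0 | −0.2; 0 | −0.2 | 0.2 / 0.5 = 40% |
| 0 | −0.1 | 0; +0.1 | −0.1 | 20% |

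The last row is the case where assignment to the low-fat diet depresses baseline performance: the apparent gain on the control diet is inflated and the Mediterranean advantage is understated. With the signs reversed, the bias runs the other way.

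For baseline adjustment, β could lie anywhere from 0 to 0.6. The upper end takes the correlation of 0.6 in section 2.7 as the slope, which the protocol does not say it is. The lower end applies if all four measurements correlate equally, because the covariance between the period difference in end scores and the period difference in baselines is then ρ − ρ − ρ + ρ = 0. A differential shift of 0.1 SD would then pass through as 0 to 0.06 SD, and one of 0.2 SD as 0 to 0.12 SD.

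**4. Which outcomes are touched**

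Only cognitive outcomes tested at the clinic visits. Home blood pressure, SF-36 and POMS are collected in the week before each phase, ahead of that phase's assignment step and session.

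**The case against.** The strongest reply is that the order rests on one connective in a condensed article. Breakfast and cognitive testing take place at all four visits, so the sentence that contains it cannot belong to Weeks 0 and 16 alone. It may simply resume the list of visit content. The section devoted to cognitive procedure has breakfast following the clinical measurements and mentions no counselling. This justifies calling the point a matter to reconcile. It does not remove the point, because nothing in the article puts the dietitian session after testing and the only order given puts it before.

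A reader might also infer more than the text supports:

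- **That the two sections flatly contradict each other.** They do not: every listed standardisation item can hold under either order.
- **That the diet comparison is biased.** Both diets follow the same order, so a common shift cancels. A diet-dependent shift is possible, but nothing in the document shows one, and the article does not commit to change scores. How baseline enters the model may properly be left to the analysis plan.
- **That the order mimics improvement.** This would require the preceding steps to lower baseline scores, which is not established. Participants also know their diet at the end of each phase, so knowing it at baseline could make expectation more alike at the two time points.
- **That both baselines could be taken blind to allocation.** In a 2 × 2 crossover, a participant told the design can infer the second diet, so this is achievable only at Week 0. At Week 16 the avoidable element is the session before testing.

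**Conclusion.** The point holds in a limited form. On the order as written, the cognitive baselines at Weeks 0 and 16 follow diet assignment and a 45-min diet-specific session that have no described counterpart at Weeks 8 and 24, and the standardisation statement leaves those steps unplaced. A common shift would bias within-phase change in cognition and nothing between diets. A diet-dependent shift would bias between-diet comparisons to the extent that they use these baselines.

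Direction and size cannot be determined from the document; the percentages above only illustrate assumed shifts. End-of-phase comparisons and the primary outcome are unaffected. The conclusion rests on reading section 2.6 as a sequence and on the absence of any comparable session before testing at Weeks 8 and 24. It is worth correcting because it removes an avoidable ambiguity in secondary outcomes by reordering a visit that already takes place.

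**What to change.** Reconcile section 2.6 (Procedure) with its Cognitive Measures part by stating one sequence for Weeks 0 and 16:

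- clinical measurements, then breakfast, then cognitive testing;
- the dietitian session last, at the end of the same visit;
- at Week 0, disclosure of the allocation also held back until testing is complete.

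The steps before testing would then match those described for Weeks 8 and 24. No visit, measurement or session is added. The small cost is that the 45-min counselling follows the cognitive battery, when participants may be tired. The article does not give visit timings, so the site should confirm that the visit still fits.

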#### Cognitive Measures

A computerised mode of cognitive testing has been chosen to increase accuracy and reliability in detecting change, especially in instrument sensitive tasks such as reaction time [151]. To limit the influence of potential measurement bias, the administration of cognitive measures will be controlled and standardised across participants and visits, as described by Stonehouse et al. [152]. Cognitive assessments at Weeks 0, 8, 16 and 24 will be conducted at a similar time of day, between 9:30 a.m. and 12:00 p.m. Participants will have completed a 12-h fast from food, beverages (excluding water), caffeine and alcohol before arriving at the clinical trial facility. Following cardiometabolic assessments, anthropometry and DEXA scan, the same continental breakfast will be provided and eaten within 15 min of cognitive testing. If participants have not had an adequate amount or quality of sleep the preceding night cognitive testing will be rescheduled. The testing environment will be controlled with regard to temperature and noise in order to reduce distraction. A CANTAB familiarisation task will be performed at each testing session, and each cognitive task will have a practice component. Further, CANTAB administration will be standardised through use of a testing script provided by Cambridge Cognition.

